## Abstract

**Background:**

Acupuncture is a popular non-pharmacological modality for treating musculoskeletal pain. Physiotherapists are one of the largest groups of acupuncture providers within the NHS, and they commonly use it alongside advice and exercise. Conclusive evidence of acupuncture's clinical effectiveness and its superiority over sham interventions is lacking. The Arthritis Research Campaign (**arc**) has funded this randomised sham-controlled trial which addresses three important questions. Firstly, we will determine the additional benefit of true acupuncture when used by physiotherapists alongside advice and exercise for older people presenting to primary care with knee pain. Secondly, we will evaluate sham acupuncture in the same way. Thirdly, we will investigate the treatment preferences and expectations of both the participants and physiotherapists participating in the study, and explore the effect of these on clinical outcome. We will thus investigate whether acupuncture is a useful adjunct to advice and exercise for treating knee pain and gain insight into whether this effect is due to specific needling properties.

**Methods/Design:**

This randomised clinical trial will recruit 350 participants with knee pain to three intervention arms. It is based in 43 community physiotherapy departments in 21 NHS Trusts in the West Midlands and Cheshire regions in England. Patients aged 50 years and over with knee pain will be recruited. Outcome data will be collected by self-complete questionnaires before randomisation, and 6 weeks, 6 months and 12 months after randomisation and by telephone interview 2 weeks after treatment commences. The questionnaires collect demographic details as well as information on knee-related pain, movement and function, pain intensity and affect, main functional problem, illness perceptions, self-efficacy, treatment preference and expectations, general health and quality of life. Participants are randomised to receive a package of advice and exercise; or this package plus real acupuncture; or this package plus sham acupuncture. Treatment details are being collected on a standard proforma. Interventions are delivered by experienced physiotherapists who have all received training in acupuncture to recognised national standards. The primary analysis will investigate the main treatment effects of real or sham acupuncture as an adjunct to advice and exercise.

**Discussion:**

This paper presents detail on the rationale, design, methods, and operational aspects of the trial.

## Background

Knee pain in older adults is a common disabling problem. Approximately 25% of the population aged over 55 years are affected at any one time and half of these will have some restriction of normal daily activities [1,2]. After excluding `red flags' and specific pathologies such as inflammatory arthritis, most knee pain in older adults is due to osteoarthritis. Controlling the pain and minimising loss of function are the principal aims of treatment. Most sufferers are managed exclusively in primary care [3-5], where the usual approaches include analgesics and exercise [6-11]. A report from Arthritis Care [12] of patients' perspectives highlighted that people with knee osteoarthritis want treatment offering more pain relief and help with mobility. Easy to understand information was also felt to be important, as was exercise, to help manage the problem. A recent review of international guidelines suggests that, for patients with knee pain, the best non-pharmacological care consists of education, muscle strengthening and exercise [13].

Patients with musculoskeletal pain often choose methods of treatment that are not widely available within the NHS, such as complementary medicine [14]. Reports from the United States and the United Kingdom have indicated the popularity of complementary medicine with the general public and health care professionals [15-19]. Complementary medicine is available in approximately 40% of general practice surgeries and general practitioners and physiotherapists are the largest providers of complementary medicine within the NHS [17]. Acupuncture is one of the most popular complementary medicine modalities in the UK: reports suggest that it is available in 84% of chronic pain clinics and approximately 4000 general practitioners and physiotherapists are trained in acupuncture [21,22]. Although recent authors have promoted the concept of integrated practice incorporating conventional and complementary therapies [20], current guidelines highlight the need for further research evidence for the use of acupuncture for knee pain in older adults [13]. The clinical effectiveness of acupuncture, and the question of whether it is superior to sham interventions has not been established. In addition to providing exercise and advice, physiotherapists are also one of the largest groups of acupuncture providers within both primary and secondary care in the NHS [23]. Physiotherapy is therefore an appropriate and important arena in which to investigate the effectiveness of integrated mainstream and complementary therapy.

## Evidence for advice and exercise

International guidelines suggest that the best package of care for this patient group is one that includes patient education, advice and exercise [13]. There is strong evidence for the usefulness of education, muscle strengthening and aerobic exercise. The beneficial effects of exercise on knee pain are well documented and it is a key component of successful rehabilitation programmes for patients [24,25]. Active rehabilitation programmes for patients with musculoskeletal and arthritic pain not only improve joint function and reduce pain, but also improve strength, walking speed and self-efficacy [26] as well as quality of life, and they reduce risk of other chronic conditions [27]. Randomised clinical trials consistently show the benefit of exercise for knee pain in older adults [28-31]. Recent studies also highlight the need to provide adequate instruction, feedback and practice in order to ensure that the key muscle groups around the knee, such as the quadriceps, are activated [32]. The European League Against Rheumatism (EULAR) recommendations have recently been updated and in particular, advocate exercise for knee pain related to osteoarthritis [33]. In line with this evidence base, the current trial was designed so that all participants receive a package of care which includes education, advice, and exercise.

## Evidence for acupuncture

The physiological properties of acupuncture have been well described in the laboratory. Acupuncture activates central mechanisms of pain control and elicits release of specific neurotransmitters (mainly opioids) in the central nervous system [34,35]. Effects on the autonomic nervous system have also been demonstrated during and after acupuncture stimulation [36,37]. Despite this, its clinical effectiveness remains a matter of controversy [38,39]. This is partly because of methodological limitations in many trials of acupuncture, including small sample sizes, lack of credible sham-controls, and inadequate blinding [40]. Acupuncture has been shown to have a short-term analgesic effect in musculoskeletal pain [41,42]. A recent evaluation of acupuncture by the National Institutes of Health concluded that it has an analgesic effect on dental and orofacial pain and is a useful adjunct in a range of painful conditions, including musculoskeletal and myofascial pain [43]. In fibromyalgia, there is increasing evidence demonstrating the usefulness of acupuncture [44,45]. One meta-analysis concluded that acupuncture might offer benefit to patients with knee osteoarthritis when used as an adjunct to mainstream management strategies [46].

Appropriate sham interventions for acupuncture have been widely debated and several placebo needles have been introduced and tested [47,48]. A trial conducted in Germany recently concluded that true acupuncture has a better effect than sham acupuncture in the treatment of knee and back pain, but not for migraine headache [49]. In addition, another study reported positive effects of acupuncture for knee pain [50]. However, a key limitation to these studies is the lack of long-term follow-up, something which the current study has been designed to address [51].

We have designed, and are currently implementing, a prospective sham controlled randomised trial within the primary care setting addressing the important clinical question: is acupuncture a useful adjunct to physiotherapy care (advice and exercise) for treating knee pain in older adults? Research and development in primary care is important to public health and necessary to support the decisions and treatments in this setting [52].

The primary objective is to compare, at 6 months, the clinical outcomes of true acupuncture plus advice and exercise, with advice and exercise alone for treating people aged 50 years and over referred directly from primary care with knee pain. Our secondary objectives are

i) to compare, at 6 weeks and 12 months, the clinical outcomes of adding true acupuncture to advice and exercise alone, in the same patient group.

ii) to compare, at 6 weeks, 6 and 12 months, the clinical outcomes of sham acupuncture plus advice and exercise, with advice and exercise alone, in the same patient group.

iii) to measure patients and physiotherapists beliefs, preferences and expectations about the treatments being tested and to explore their effect on clinical outcome.

## Methods

### Trial design

This multicentre, three-arm sham-controlled randomised trial will be conducted in 43 individual Physiotherapy Centres that provide services for Primary Care Physicians located in 21 NHS Trusts situated in the Midlands and Cheshire regions of the UK. Multi-centre ethical approval has been obtained from the West Midlands Multicentre Research Ethics Committee and local approval was given by 12 ethics committees (Southern Derbyshire, Shropshire, Worcestershire, Warwickshire, Mid Staffordshire, South Staffordshire, Sollihull, North Birmingham, South Birmingham, West Birmingham, East Birmingham, East Cheshire). The trial was designed by a steering group with expert input from physiotherapists, an acupuncture specialist and trial methodologists. Information will be collected from the individual participating physiotherapists (demographics, current training and use of acupuncture, attitudes and beliefs about knee pain, and beliefs and expectations of the three treatment packages being compared in the trial) prior to the commencement of the trial and after the trial has been completed (Table 1).

### Study population

Participants include patients with knee pain aged 50 years and over referred to physiotherapy centres by their general practitioner. Participants will be randomised to one of three groups: (i) advice and exercise alone, (ii) advice and exercise plus true acupuncture, (iii) advice and exercise plus sham acupuncture. Follow up will be at 2 weeks (by telephone), 6 weeks, 6 months and 12 months after randomisation, by postal questionnaire. Non-responders will be followed up.

### Inclusion criteria

Eligible patients are male and female subjects aged 50 years and above with pain (with or without stiffness) in one or both knees presenting to primary care. They must be naïve to acupuncture treatment (i.e. have never experienced acupuncture before for their present or any past complaints), and considered suitable for referral to a physiotherapy outpatients department by their general practitioner. Participants must be able to read and write English, be willing to consent to participation, and able give full informed consent. They must also be available for telephone contact.

### Exclusion criteria

Patients with potentially serious pathology (e.g. inflammatory arthritis, malignancy etc) on the basis of general practice or physiotherapy diagnosis or from past medical history, those who have had a knee or hip replacement on the affected side(s), are already on a surgical waiting list for total knee replacement, or for whom the trial interventions are contraindicated are excluded from the trial. Those who have received an exercise programme, from a physiotherapist, for their knee problem within the last 3 months (normal recreational involvement in sport or exercise will not be an exclusion) or an intra-articular injection to the knee in the last 6 months are also excluded.

### Participant recruitment

Eligible patients referred by their GP to the physiotherapy departments will be invited to take part. Recruitment will take place over 18 months and will operate in one of two ways (See Figure 1):

#### 1) Trial nurse

To identify potentially eligible patients, a trial nurse will review GP referral letters received by participating physiotherapy departments that fall within a feasibly commuteable geographical area of the Research Centre.

#### 2) Local physiotherapy assessor

A minimum of two members of the physiotherapy team will be involved at centres that fall outside the trial nurse's geographical area, one will be the nominated local assessor and a second will treat participants.

The nominated local physiotherapy assessor or trial nurse will perform an initial screen of the referrals to the physiotherapy department for potential participants. Potentially eligible patients will be posted information about the study, and their GP will be notified that the patient has been approached to take part. The GP will be asked to notify the Physiotherapy Department if they feel the patient is ineligible or unsuitable.

### Consent

A minimum of 48 hours after receiving the information leaflet, patients will be telephoned by the nominated local assessor/trial nurse (within 10 working days) to further screen eligibility. Information will be recorded on a standard proforma. For those patients either not eligible or not willing to be recruited, the proforma will be used to detail the reason for ineligibility, or reason for decline. Where patients are willing, two additional questions are asked to those that decline to participate in the trial to capture their treatment preference and expectations with respect to acupuncture and an advice & exercise treatment package. This information will be anonymised.

For patients willing to be recruited to the trial, an appointment is arranged for a research assessment at the patient's local physiotherapy department. After gaining verbal consent, the patient will be posted the baseline questionnaire to complete prior to their research appointment. At the research assessment visit the local physiotherapy assessor/trial nurse will perform a more detailed eligibility screen, explain the study, gain informed written consent to randomisation and conduct a baseline research interview and examination. Following consent to the study, the participant will be registered with the Research Centre by fax and allocated a unique trial number. The baseline assessment will be carried out blind to subsequent treatment allocation. An appointment will be made for the treating physiotherapist to begin treatment within 10 working days of the research assessment. Consent to treatment will be gained from each treating physiotherapist prior to commencing treatment, as is current physiotherapy practice. All participants will have an initial clinical physiotherapy assessment and treatment session of up to 40 minutes duration. During this session the physiotherapist will identify and record potential acupuncture points to be used should the participant be randomised to receive acupuncture (true or sham). A minimum of 6 and maximum of 10 points will be selected, based upon the participant's presentation and the clinical opinion of the physiotherapist. This will be carried out as part of the overall physical examination of the knee – the therapist will not draw the participant's attention to the localisation of acupuncture points to avoid raising their expectations about the possibility of receiving acupuncture. The advice and exercise package will then be started during this initial treatment visit.

### Randomisation

Randomisation will take place after this initial physiotherapy session. The treating physiotherapist will telephone the Research Centre at Keele University, during normal working hours. This methodology ensures that the initial physiotherapy assessment and advice and exercise package provided is performed blind to subsequent treatment allocation. The specific trial interventions will commence during the participant's second treatment visit. During the randomisation telephone call the physiotherapist will be asked to identify the selected acupuncture sites to check that the participant has received their first pre-randomisation treatment session. The physiotherapists will also be asked questions about their own expectations of the individual participant's likely clinical outcome and their beliefs about which treatment they would like the participant to receive. Participants recruited to the trial will then be randomised to one of the three trial interventions in a 1:1:1 ratio based on their unique trial number. Computerised third-party randomisation will be performed using random permuted blocks of 12 (blocked by treatment centre).

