### Sample size calculation

The primary outcome measure for this trial is the Western Ontario and McMaster Universities Osteoarthritis Index (WOMAC) pain sub-scale [61]. We have defined overall success as a 20% difference in the WOMAC pain sub-scale between true acupuncture and advice and exercise alone at 6 months. For this comparison, a minimum of 90 participants is needed in each group to reject the null hypothesis with 80% power and at a 5% significance level (two-tailed) [68]. As our trial will compare sham acupuncture with advice and exercise alone we have three groups and so need 270 participants. Allowing for a 30% drop out rate in those recruited to the trial, the total number of participants required to be randomised is 350.

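### A single, disclosed block length of 12 within each centre leaves modest predictability for the unblinded treating physiotherapist, so blindness of the first session is not fully ensured

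*Protocol article*

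**What the plan says.** The Randomisation section of the protocol article fixes the scheme: "Computerised third-party randomisation will be performed using random permuted blocks of 12 (blocked by treatment centre". Participants are "randomised to one of the three trial interventions in a 1:1:1 ratio based on their unique trial number", so each block holds four places per arm. The treating physiotherapist makes the call, after the first treatment session. Of this arrangement the section says: "This methodology ensures that the initial physiotherapy assessment and advice and exercise package provided is performed blind to subsequent treatment allocation".

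During the same call, before the arm is given, the physiotherapist states the outcome expected for this participant and the treatment they would like the participant to receive.

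On staffing, the section on the local physiotherapy assessor sets a minimum of two team members at centres outside the trial nurse's area: "one will be the nominated local assessor and a second will treat participants". The Consent section places written consent and the baseline interview and examination at the research visit, with the questionnaire filled in beforehand. Following consent, "the participant will be registered with the Research Centre by fax and allocated a unique trial number". All of this comes before the first treatment session.

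The Background (Evidence for acupuncture) describes the trial as being implemented at the time of writing. The article does not say that the block length is varied or kept from the centres.

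**The concern.** A third-party telephone service hides the list. Calling after the first session delays disclosure. Neither stops someone who knows the block length and the centre's past allocations from counting the places left. Here the length is one fixed number, it is printed in the article, and the person who learns each allocation is the person who conducts the next participant's first session.

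Two things are exposed without any communication between staff:

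- **The first advice-and-exercise session**, including the selection of points. The baseline questionnaire is completed before this session, so adjusting for baseline would not correct a session shaped by a guess about the coming arm.
- **The physiotherapist's expectation and preference ratings**, which serve secondary objective iii. They are meant to be given in ignorance of the arm.

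A third route, selection at enrolment, is weaker. It needs the local assessor to learn past allocations from the treating colleague, and the article does not say that this happens.

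**Working it through.** The article states no predictability figure, so there is none to reproduce.

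**Inputs from the article.** Block length 12, ratio 1:1:1, hence 4 + 4 + 4 (Randomisation). Total randomised: "the total number of participants required to be randomised is 350" (Sample size calculation). Centres: "It is based in 43 community physiotherapy departments in 21 NHS Trusts" (Abstract). Mean size is 350/43 = 8.1 per department, less than one block. If treatment centre meant the Trust, it would be 350/21 = 16.7.

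**Assumptions.** The guesser knows the centre's whole history in list order and always names the arm with most places left. Centre sizes are not given, so three patterns are used: 8-9 in every centre; sizes varying at random with equal recruitment rates; and skewed sizes (lognormal rates, log-SD 1).

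**Certain allocations within a block of 12.** The next allocation is certain only if all remaining places belong to one arm. With r places left, and r at most 4, the probability is 3 × C(4, r) / C(12, r).

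| Position | Places left (r) | Probability that it is certain |
|---|---|---|
| 9 | 4 | 3 × 1/495 = 0.6% |
| 10 | 3 | 3 × 4/220 = 5.5% |
| 11 | 2 | 3 × 6/66 = 27.3% |
| 12 | 1 | 100% |

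Before position 9 certainty is impossible. A completed block has 0.006 + 0.055 + 0.273 + 1 = 1.33 certain allocations, or 1.33/12 = 11.1%.

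**Correct guesses.** By exact enumeration the best guess at positions 1 to 8 is right with probability 0.333, 0.364, 0.400, 0.412, 0.427, 0.459, 0.476 and 0.497. For a centre of 8 the mean is 3.368/8 = 42.1%. The rate reaches 63.6% at position 11.

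**Averaged over 350 participants in 43 centres.**

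| Centre sizes (assumed) | Correct guess | Certain | At least one arm ruled out |
|---|---|---|---|
| 8-9 each | 42% | about 0% | about 5% |
| Equal rates | 44.0% | 2.4% | 11.3% |
| Skewed | 45.7% | 5.5% | 16.6% |
| Unpredictable list | 33.3% | 0% | 0% |

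At equal rates 12% of centres reach 12 participants; with skewed sizes 22% do. If the centre were the Trust, with 17 participants, certainty would be 1.33/17 = 7.8% and the correct-guess rate about 47.5%.

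**Alternatives within centre.** Guessing the least-used arm over a centre's first 8 participants is right for 42.0% with fixed 12, 40.1% with random 12/15/18 and 46.7% with random 6/9/12. Over all 350 participants, 9/12/15 gives 43.8% (8-9 each) and 46.1% (skewed, exponential sizes), against 42.2% and 45.8% for fixed 12. In a further simulation of 12/15/18 over the three size patterns in the table, certain allocations were 0%, 0% and about 0.6%, even for an observer who knows the set of lengths. The guess rate fell by about 1.5 to 2 points.

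**The case against.** The safeguards are substantial. Randomisation is computerised and held by a third party. The arm is disclosed only after consent, registration, baseline measures and the first session. The enroller is the trial nurse or an assessor who is not the treating physiotherapist. Twelve is four times the number of arms, a reasonable compromise between concealment and balance, and most centres will not complete a block. The guess rates are a ceiling: they need full knowledge and optimal counting. All of this stands, and it keeps the point modest.

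Four stronger readings are tempting but not supported:

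- **That centre staff see every past allocation.** The article shows this only for a physiotherapist's own participants. It covers the whole centre where one person treats everyone, which minimum staffing permits, or where colleagues share what they know. Nothing says that the assessor is told the arm.
- **That tying allocation to the trial number breaks concealment.** An arm already fixed on a hidden list unblinds nobody. If calls arrive out of trial-number order, guessing becomes harder.
- **That the primary comparison is biased by a stated amount.** Any figure needs an assumed shift in case mix or care for each guess, and the documents supply none.
- **That the analysis could neither detect nor repair the effect.** Baseline measures are taken before allocation, and the Analysis section provides for inspecting important differences and using them as covariates. That covers measured case-mix shifts, though not unmeasured ones or an altered first session.

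The article also does not show that recruitment was still open when it appeared, only that the trial was being implemented.

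**Conclusion.** The point holds in a limited form. A fixed, disclosed block length within centres, with an unblinded treating physiotherapist, allows guessing at about 42-46% against 33%, and certainty for about 0-6% of allocations. Both ranges rest on assumed centre sizes and on full knowledge of the centre's history, and would be somewhat higher if the centre were the Trust. The word *ensures* therefore promises more than the method can give for the first session, and the pre-allocation ratings share the weakness. This does not show that concealment fails or that the primary result is biased. It is a minor to moderate weakness with a cheap remedy.

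**What to change.** For blocks not yet started:

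1. Keep blocking by centre, but draw each block length at random from lengths no shorter than 12, for example 12, 15 and 18.
2. Withhold the lengths from centres, and from publications while recruitment is open.
3. In the Randomisation section, replace *ensures* with a statement that the first session is completed before the allocation is disclosed.

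Shorter mixed lengths such as 6/9/12 should be avoided because they raise the average guess rate; 9/12/15 leaves it about where it is.

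The cost is a small reprogramming task and slightly looser balance. In the simulation the mean gap between the largest and smallest arm in a centre rose from about 1.4-1.6 to 1.5-1.8 participants. If recruitment has already closed, only the wording change applies.

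Replacing centre blocks with one central list is not part of this fix. It would bring guessing down to about 33-34%, but in a centre of 8 the chance that an arm is missing altogether would rise from 3/495 = 0.6% to about 3 × (2/3)^8 = 12%. That is a trade-off where therapists in 43 departments deliver the treatment.

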### Analysis

Collection of data and statistical analysis will be performed blinded to treatment allocation. Analysis will be performed on an intention to treat basis and the primary outcome will also be analysed on a "per protocol basis".

Univariate analysis will be performed using t-tests to analyse numerical data and chi-square tests for categorical data. The clinical and demographic data collected at baseline will be inspected and if there are any important differences between the trial groups, these factors will be used as covariates. These analyses will be performed using ANOVA and logistic regression as appropriate.

The analysis of the secondary outcomes will be exploratory. A univariate analysis with respect to the different treatment will be performed for the WOMAC pain sub-scale at 6-weeks and 12-months and for the WOMAC functioning sub-scale at 6-weeks, 6- and 12-months. The global outcome assessment with be analysed both as an ordinal and a dichotomous variable (categories 1–3 defined as "success"). Moreover, area under the curve slopes will be calculated for each treatment group over the whole treatment period and compared.

Statistical significance will be set at the 5% level (two-tailed). Statistical analysis will be performed using Stata 7.0. The trial will be monitored by an independent Data Monitoring and Ethics Committee. No interim analysis of the primary or secondary outcomes will be undertaken during the trial period.

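### Randomisation is blocked by treatment centre but the stated tests ignore centre, which makes them conservative and costs some power if outcomes differ between centres

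*Protocol article*

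**What the plan says.** The Trial design section of the protocol article states that the trial "will be conducted in 43 individual Physiotherapy Centres". The Randomisation section has participants "randomised to one of the three trial interventions in a 1:1:1 ratio", using "random permuted blocks of 12 (blocked by treatment centre". No other stratification factor is named.

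The Analysis section fixes the tests: "Univariate analysis will be performed using t-tests to analyse numerical data and chi-square tests for categorical data". Covariates enter by a conditional rule, which rests on looking over the baseline clinical and demographic variables: "if there are any important differences between the trial groups, these factors will be used as covariates". ANOVA or logistic regression is then used. On the error rate it says "Statistical significance will be set at the 5% level (two-tailed". Centre does not appear in the Analysis section as a covariate, a stratum or a random effect.

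**The concern.** Blocking within centre makes the arms more alike in their mix of centres than simple randomisation would. The treatment difference then varies less from trial to trial, provided outcomes differ between centres. A two-sample t-test does not know this. It leaves all between-centre variation in the error term and reports a standard error that suits an unstratified allocation. The design buys some precision and the analysis does not use it.

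The covariate rule does not close the gap. Centre is neither a clinical nor a demographic baseline variable, and a factor balanced by design would seldom be flagged as an important difference between groups.

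Some variation between centres is plausible. The Interventions section has the treating physiotherapist individualise the exercises and choose the acupuncture points. At stake are confidence intervals that are too wide and a somewhat higher chance of missing a real effect.

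**Working it through.** **Inputs from the protocol article.** 350 randomised, 1:1:1, 43 centres, blocks of 12 within centre, 30% drop-out, two-sided 5%, 80% power with 90 per group. **Assumed:** the centre ICC, which the documents do not give, ranged from 0 to 0.20.

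**1. The plan's own figure.** Sample size calculation says "a minimum of 90 participants is needed in each group to reject the null hypothesis with 80% power and at a 5% significance level". No standard deviation or reference mean is given, so 90 cannot be rebuilt from stated inputs. Solving backwards, the implied standardised difference is (1.960 + 0.842) × √(2/90) = 0.418. This is the effect size used below.

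**2. Centre size against block size.** 350/43 = 8.1 randomised per centre. After 30% loss, 350 × 0.70 = 245, and 245/43 = 5.7 analysable per centre. An average centre does not complete one block of 12, so balance by centre is only partial.

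**3. Bound.** Set the total variance to 1 and the ICC to ρ, with n per arm. The t-test estimates the variance of the difference as about 2/n. With perfect balance within centres the true variance is 2(1 − ρ)/n. The reported standard error is then too large by 1/√(1 − ρ), and the actual type I error is 2[1 − Φ(1.96/√(1 − ρ))].

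- ρ = 0.05: ratio 1.026, type I error 4.4%
- ρ = 0.10: ratio 1.054, type I error 3.9%
- ρ = 0.20: ratio 1.118, type I error 2.8%

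With no balance at all the ratio is 1 and the error is 5%. This design lies between the two.

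**4. The design as stated, t-test ignoring centre.** 6,000 simulated trials per row, 43 equal or unequal centres, blocks of 12. Loss was set at 23%, so that about 90 per arm are analysed (350 × 0.77/3 = 89.8).

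| Assumed ICC | Mean reported SE / true SE | Type I error |
|---|---|---|
| 0 | 0.99–1.00 | 5.5–5.7% |
| 0.01 | 0.99–1.00 | 5.0–5.3% |
| 0.05 | 1.01–1.02 | 4.5–4.7% |
| 0.10 | 1.03–1.04 | 4.1–4.2% |
| 0.20 | 1.06–1.07 | 3.5–3.6% |

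Simulation error is about √(0.05 × 0.95/6000) = 0.3 points. The first two rows show no mismatch, and the drop at 0.05 is barely larger than that error.

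**5. Random centre intercept, ICC estimated by REML.** 4,000 trials per row, unequal centres, the full 30% loss (245/3 = 81.7 per arm), difference 0.418.

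| Assumed ICC | Type I error, t-test → mixed model | Power, t-test → mixed model |
|---|---|---|
| 0 | 5.3% → 5.3% | 75.1% → 75.2% |
| 0.05 | 4.8% → 5.2% | 75.0% → 76.0% |
| 0.10 | 4.4% → 4.9% | 75.5% → 78.2% |
| 0.20 | 3.6% → 4.6% | 76.0% → 81.8% |

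The gains are 0.1, 1.0, 2.7 and 5.8 points. A second REML run of the same design gave 1.4, 2.5 and 5.8 points at the three positive ICCs. Across all runs, t-test type I error at ICC 0.20 ranged from 3.5% to 4.2%, so no single value should be read as precise.

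**6. Fixed centre effects instead** (setting of step 4). Power of the t-test against the fixed-effects model:

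- ICC 0: 80–81% against 74–75%
- ICC 0.05: 80–81% against 76%
- ICC 0.10: 80–81% against 77–78%
- ICC 0.20: 81% against 83%

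Fixed effects lose power unless the ICC is high.

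**The case against.** The strongest reply is that this is a small matter of efficiency in a condensed journal article. The Analysis section does not exclude centre, it already allows regression models, and a full protocol or analysis plan might add the stratification factor. The primary outcome comes from self-completed postal questionnaires rather than centre assessors, and treatment follows common protocols, so the ICC may be low. The staffing stated under Participant recruitment is only a minimum, and only for centres outside the nurse's area, so it does not show that each centre has few therapists. At ICC 0.05 the gain is about one point of power.

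Most of this stands, and it limits the size of the point. It does not remove it: the article names the tests and the adjustment rule, and as written they leave out the factor used to randomise.

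Three stronger readings are tempting, and the documents do not support them.

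- A reader might infer that p-values which do not match the design can produce false positives or a biased estimate. The mismatch runs the other way, towards caution, and no bias follows from it.
- A reader might infer that incomplete blocks make matters worse. They bring the allocation closer to simple randomisation, where the t-test is correct, and so reduce the mismatch. The noise they leave behind is minor: in one REML run, adjusting for centre cut the true sampling SD of the treatment estimate by only about 0%, 1% and 3% at ICC 0.05, 0.10 and 0.20. Most of the power gain comes from removing the conservatism.
- A reader might assume that baseline WOMAC is already a fixed covariate, to which centre need only be added. The Analysis section pre-specifies no such covariate, and the figures above are for centre alone.

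**Conclusion.** The point holds as one of efficiency, not validity. The stated analysis ignores the only stratification factor. If outcomes vary between centres, the t-test is conservative, with type I error of about 4.5–4.8%, 4.1–4.4% and 3.5–4.2% at ICC 0.05, 0.10 and 0.20. The power given up is about 1, 3 and 6 points. At an ICC of 0.01 or less nothing is detectable. These sizes rest on an ICC that the documents do not give, on a standardised difference of 0.418 inferred from the stated 90 per group, and on simulated centre sizes. The direction does not depend on the exact ICC, provided it is above zero. The change is worth making because it is nearly free and cost no detectable power or type I error in simulation when centre effects were absent.

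**What to change.** In the Analysis section, pre-specify treatment centre as a random intercept in the primary model for WOMAC pain at 6 months, whatever differences are seen at baseline. Use the same term in the corresponding secondary models; this matters less there, because those analyses are labelled exploratory. Prefer a random intercept to 42 fixed effects: with about 6 analysable participants per centre, fixed effects lost roughly 2 to 7 points of power at ICC 0.10 or less.

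The cost is one extra model term, using information the trial already holds in order to randomise. If centre effects turn out small, little is gained.
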